## Abstract

Parkinson’s disease (PD) and multiple sclerosis (MS) are two chronic neurological diseases (CNDs) that have a high demand for early and continuous rehabilitation. However, accessing professional care remains a challenge, making it a key priority to identify sustainable solutions for ensuring early rehabilitation availability. **Objective**: The FIT4TeleNEURO pragmatic trial proposes to investigate, in real-life care settings, the superiority in terms of the effectiveness of early rehabilitation intervention with harmonized, mix-model telerehabilitation (TR) protocols (TR single approach, task-oriented—TRsA; TR combined approach, task-oriented and impairment-oriented—TRcA) compared to conventional management (control treatment, CeT) in people with PD and MS. **Design, and Methods**: This multicenter, randomized, three-treatment arm pragmatic trial will involve 300 patients with CNDs (PD, N = 150; MS, N = 150). Each participant will be randomized (1:1:1) to the experimental groups (20 sessions of TRsA or TRcA according to a mix-model—3 asynchronous + 1 synchronous session/week) or the control group (20 sessions of CeT). Primary and secondary outcome measures will be obtained at the baseline (T0), post-intervention (T1, 5 weeks after baseline), and follow-up (T2, 3 months after the end of the treatment). A multidimensional evaluation (cognitive, motor, and quality of life domains) will be conducted at each time point of assessment (T0; T1; T2). The primary outcome measures will be the assessment of change (T0 vs. T1 vs. T2) in static and dynamic balance, measured using the Mini-Balance Evaluation Systems Test. Usability and acceptability assessment will be also investigated. **Expected Results**: Implementing TR protocols will enable a more targeted and efficient response to the growing demand for rehabilitation in the early stages of CNDs. Both the TRsA and TRcA approaches are expected to be more effective than CeT, with the combined approach likely providing greater benefits in secondary outcome measures. Finally, the acceptability of the asynchronous modality could open the door to scalable solutions, such as digital therapeutics.

## 1. Introduction

Chronic neurological disorders (CNDs) are the second leading cause of death worldwide [1]. Due to their progressive nature and neurodegenerative characteristics, these disorders often lead to long-term disabilities that affect physical, cognitive, behavioral, and social functioning [2]. While pharmacological interventions play a crucial role, rehabilitation strategies are essential for managing disability, particularly when implemented from the early stages of the disease.

Parkinson’s disease (PD) and multiple sclerosis (MS) are among the CND conditions with the highest demand for rehabilitation. Despite differing in etiopathogenetic mechanisms, both disorders share a progressive neurodegenerative course and common rehabilitative objectives, such as improving functional mobility and physical capacity [3,4,5,6]. These areas benefit significantly from rehabilitation, especially when treatment is initiated early and delivered intensively [7,8,9,10]. Early, intensive, and accessible interventions have been shown to enhance exercise tolerance, walking ability, and balance [11,12,13], while significantly reducing the risk of falls, a critical concern for these patients [14,15,16].

As highlighted by Cieza and colleagues [17] in their analysis of the Global Burden of Diseases, Injuries, and Risk Factors Study (GBD 2019), an estimated 2.41 billion individuals (95% uncertainty interval 2.34–2.50 billion) worldwide could benefit from rehabilitation services. This vision challenges the misconception that rehabilitation is a niche service required by only a small segment of the population. The authors further argue that rehabilitation must be integrated into primary healthcare systems to ensure equitable access, particularly for underserved communities. In the context of the Italian National Health Service, equitable access to rehabilitation remains a significant challenge. Patients in the early stages of chronic disability are particularly affected, as no standardized care pathways exist to ensure timely and continuous management of their needs. Addressing this gap by developing sustainable and effective solutions for early access to rehabilitation services for CND patients is an urgent priority.

Technological advancements in healthcare, as highlighted by Topol [18], provide an opportunity to transform the healthcare system and care delivery, with digital medicine and telemedicine playing a pivotal role in this transition. Among telemedicine applications, telerehabilitation (TR) has emerged as a promising approach for delivering integrated, continuous care for individuals with chronic neurological disabilities from the earliest stages [19,20,21]. Research has demonstrated the feasibility of TR interventions for various CNDs, including MS [22,23,24,25,26,27,28] and PD [29,30,31,32,33,34,35,36,37], as well as conditions within the Alzheimer’s disease continuum [38,39]. These studies suggest that TR can achieve clinical outcomes and medical benefits comparable to traditional rehabilitation methods. However, limitations such as heterogeneous intervention protocols, small sample sizes, and a lack of standardized approaches remain challenges.

Task-oriented training is the predominant rehabilitation approach employed in the early stages of CNDs to enhance functional mobility and physical capacity. Additionally, growing evidence suggests that integrating task-oriented strategies with impairment-oriented activities may result in superior outcomes [40,41,42]. However, there remains a lack of standardized approaches in both TR and conventional care, underscoring the urgent need to establish consistent and evidence-based protocols.

The FIT4TeleNEURO study aims to implement a harmonized, multicenter TR protocol specifically designed for the early stages of PD and MS to address gait and balance difficulties at home. The study will evaluate whether this TR protocol is acceptable and effective through a pragmatic trial design, assessing its superiority over conventional care in early rehabilitative management. Furthermore, secondary objectives include examining the specific effects of rehabilitative strategies by comparing task-oriented and combined task- and impairment-oriented approaches on motor, cognitive, and quality-of-life outcomes, as well as investigating the differential impact of these digital interventions on MS and PD cohorts.

## 2. Materials and Methods

The study protocol has been developed in accordance with the guidelines outlined in the Standard Protocol Items: Recommendations for Interventional Trials (SPIRIT) (Figure 1). The study will be conducted according to the Declaration of Helsinki 2024 [43].

### 2.1. Trial Design and Setting

This pragmatic study is designed as a single-blinded, randomized, three-treatment-arm (1:1:1) study involving chronic outpatients from neurorehabilitation units of 10 FIT4TeleNEURO Centers: (1) IRCCS Fondazione Don Carlo Gnocchi ONLUS, Milano (MI); (2) IRCCS Fondazione Don Carlo Gnocchi ONLUS, Roma (RO); (3) IRCCS Fondazione Mondino, Pavia (PV); (4) IRCCS Istituti Clinici Scientifici Maugeri, Bari (BA); (5) IRCCS Istituti Clinici Scientifici Maugeri, Milano (MI); (6) IRCCS Istituti Clinici Scientifici Maugeri, Pavia (PV); (7) IRCCS Istituti Clinici Scientifici Maugeri, Montescano (PV); (8) IRCCS Istituti Clinici Scientifici Maugeri, Telese (BN); (9) Università di Modena e Reggio Emilia, Modena (MO); and (10) Ospedale Valduce, Centro di Riabilitazione “Villa Beretta”, Como (CO).

Following enrollment and the baseline assessment, each participant will be randomly assigned into one of the following three groups, with an allocation ratio of 1:1:1: (1) telerehabilitation single approach (TRsA, experimental group); (2) telerehabilitation combined approach (TRcA, experimental group); or (3) conventional educational treatment (CeT, placebo comparator).

Randomization will be stratified based on both the clinical center and the clinical conditions (MS, PD). Primary and secondary outcome measures will be collected at baseline (T0), post-intervention (T1, 5 weeks after baseline), and at follow-up (T2, 12 weeks after treatment completion). The trial work plan is shown in Figure 2.

### 2.2. Sample Size

The sample size was determined a priori using G*Power 3 software, based on previously published preliminary data [30] related to the study’s primary outcome, the Mini-Best test. Assuming a minimal clinically important difference (MCID) of 3 points (ds group 1 = 5.75, ds_group 2 = 5.98), a statistical power of 80% (type I error rate of 0.05), and an allocation ratio of 1:1:1, 48 subjects per group are required. These groups include TR with single approach (TRsA) and the control group. A third group (TR with combined approach, TRcA) of 48 subjects will be recruited to assess whether a neuromotor rehabilitation program combining two approaches (task-oriented and impairment-oriented) is superior to the control group and differs from the TRsA group in secondary outcomes. The study will recruit 144 patients with Parkinson’s disease and 144 patients with multiple sclerosis. To account for a potential 5% drop-out rate per pathology group, a total of 300 subjects will be enrolled.

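### The 48 per group matches only an undeclared one-sided 5% test; at two-sided 5% the power within each disease is about 70%, not 80%

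*Protocol article*

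**What the plan says.** Section 2.2 (Sample Size) of the protocol article says the calculation was done in G*Power 3 from previously published data (reference 30). It assumes a "minimal clinically important difference (MCID) of 3 points (ds group 1 = 5.75, ds_group 2 = 5.98" and states that with "a statistical power of 80% (type I error rate of 0.05), and an allocation ratio of 1:1:1, 48 subjects per group are required". The two groups powered are TRsA and control; a third group of the same size is added for TRcA. The total is built separately in each disease: 3 × 48 = 144 with Parkinson's disease and 144 with multiple sclerosis, raised to 300 overall for 5% drop-out per disease group.

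The error rate is described only as a "type I error rate of 0.05", with no mention of one or two sides. Section 2.8 (Statistical Analysis) gives neither a significance level nor a direction of testing. The Introduction describes the aim as "assessing its superiority over conventional care in early rehabilitative management". It cites feasibility studies "including MS [22,23,24,25,26,27,28] and PD [29,30,31,32,33,34,35,36,37", which places reference 30 among the Parkinson's disease studies.

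**The concern.** A reader meeting a 5% type I error rate without qualification takes it as two-sided, and a superiority aim does not change that, since superiority is routinely tested two-sided. If the figure of 48 needs a one-sided 5% test, one of two things follows. Either the trial accepts a 5% chance of a false claim in favour of telerehabilitation, twice the 2.5% that a two-sided 5% test allows in that direction, without saying so. Or the trial will be tested two-sided and does not have the power it states. This calculation is the article's only justification for enrolling 300 people.

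A smaller point lies in the same sentence. The SDs come from a source listed under Parkinson's disease, yet the same 48 is applied to multiple sclerosis without saying that the variability is assumed to carry over.

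**Working it through.** **Inputs (all from Section 2.2).** Difference 3 points; SDs 5.75 and 5.98; error rate 0.05; power 80%; equal allocation; comparison TRsA against control within one disease.

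**Standardised difference.** Pooled SD = √((5.75² + 5.98²)/2) = 5.866, so d = 3/5.866 = 0.5114.

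**Normal approximation.** n per group = 2(z_α + z_power)²/d².
- One-sided 5%: 2(1.645 + 0.842)²/0.5114² = 47.3, so 48.
- Two-sided 5%: 2(1.960 + 0.842)²/0.5114² = 60.02, so 61.

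**Exact noncentral t.** Degrees of freedom 2n − 2, noncentrality d√(n/2); at n = 48 this is 0.5114 × √24 = 2.505.

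| Test | n per group | Power |
|---|---|---|
| One-sided 5% | 47 | 79.3% |
| One-sided 5% | 48 | 80.02% |
| Two-sided 5% | 48 | 69.8% |
| Two-sided 5% | 60 | 79.3% |
| Two-sided 5% | 61 | 80.0% |

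The article's figure is therefore exactly the smallest n for a one-sided test.

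**Other routes to 48.** None of these two-sided or multi-group variants on the stated inputs gives 48:
- a single SD of 5.75 or 5.98, two-sided: 59 or 64;
- a rank test, two-sided: 64 or 71, depending on the assumed efficiency;
- a three-group analysis of variance: 57 to 75;
- two-sided 2.5% (Bonferroni for two comparisons): 73.

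**Size of the shortfall.**
- 48 is (61 − 48)/61 = 21% below the two-sided requirement.
- After drop-out: 150/3 = 50 per group, and 50 × 0.95 = 47.5, giving 69.4%.
- With 48 per group, 80% two-sided power is reached at a difference of 3.39 points, or for 3 points at an SD of about 5.19.
- Enrolling to the two-sided requirement would mean 3 × 61 = 183 per disease, 366 in total, and 183/0.95, rounded up to 193 per disease, with drop-out.

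**What baseline adjustment could recover.** If the quoted SDs are cross-sectional and the analysis adjusts for T0, the residual SD is 5.866 × √(1 − ρ²), where ρ is the T0–T1 correlation. Two-sided power at 48 per group is then:

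| ρ | Power |
|---|---|
| 0 | 69.8% |
| 0.40 | 77.2% |
| 0.46 | 79.8% |
| 0.47 | 80.2% |
| 0.50 | 81.7% |

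The article gives no correlation and its calculation uses none, so ρ here is an assumption.

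**The case against.** Four points can be made for the plan.

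- **The arithmetic is not wrong in itself.** A one-sided 5% test does have a 5% type I error rate, and the aim is worded directionally. That is true, but an undeclared one-sided 5% test is not what the sentence conveys. Nothing in the article states or justifies one.
- **Section 2.8 does not commit to two-sided testing, and an analysis plan not shown may settle the matter.** This also stands: a conflict between design and analysis can only be inferred from convention. The finding does not need that conflict. The article itself prints 48 as the number required for 80% power, and this is either unexplained or incorrect however the analysis plan reads.
- **Pooling both diseases gives 96 per arm and about 94% two-sided power for 3 points under the same SDs, and the model in Section 2.8 lists no disease factor.** That is correct for a pooled test. Section 2.2, however, builds its numbers and its drop-out allowance within each disease, so its 80% is a within-disease claim. The pooled figure answers a different calculation.
- **Baseline adjustment or a longitudinal model may restore the power.** It may, given a moderate correlation. That is a reason to write the assumption down, and the calculation does not carry over as it stands if the SDs are those of change scores.

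**Conclusion.** The concern holds. The stated inputs yield 48 per group only under a one-sided 5% test that the article does not declare. Under a two-sided 5% test the unadjusted comparison of TRsA with control within one disease has about 70% power (69.8%, or 69.4% after drop-out), roughly 10 percentage points below the stated 80%. The figures assume normal outcomes and take the quoted SDs as the SDs of the analysed quantity. For multiple sclerosis they further assume that the Parkinson's disease SDs apply. They do not describe a pooled analysis of both diseases. The arithmetic is certain; what remains unknown is which test the trial intends.

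**What to change.** Reword Section 2.2 as follows:

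1. Say that the test is two-sided at 5%, and replace the power claim: 48 per group gives about 70% for an unadjusted 3-point comparison within each disease.
2. If the primary analysis will adjust for baseline, give the power of that analysis with its assumed T0–T1 correlation and the source of that value. If the SDs are cross-sectional, about 0.47 or more restores 80% at 48 per group. Say whether the quoted SDs are cross-sectional or of change.
3. State that the SDs come from a Parkinson's disease study and are assumed to hold in multiple sclerosis.
4. State that the power refers to the comparison within each disease.

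If a one-sided 5% test really is intended, Section 2.2 must say so, justify it, and make clear that the false-positive rate in the favourable direction is 5%.

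The cost is rewording. Enrolment need not change if the sponsor accepts about 70% unadjusted power or can support the correlation. Holding to 80% without adjustment would require 61 per group in each disease.

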### 2.3. Study Population, Recruitment, and Randomization

Based on the sample size calculation, the trial intends to recruit 300 individuals with CND, comprising 150 diagnosed with PD and 150 with MS. Recruitment will be competitive across participating centers. Eligible patients who meet all inclusion criteria (outlined in the section below) will be randomized through a web-based allocation concealment method, using a computer algorithm created by an independent statistician. Stratified randomization will be utilized to prevent imbalances between treatment groups. Participants will be stratified according to their clinical center and condition (MS, PD) and then randomly assigned (1:1:1) to one of the experimental groups (TRsA or TRcA) or the control group (CeT) (Figure 3). The intervention will not be blinded for either clinicians or patients due to its nature. However, clinical endpoints and data collection from clinical/psychological questionnaires will be blinded for examiners/assessors. The statistician conducting the data analysis will also be blinded to group allocation.

### 2.4. Inclusion and Exclusion Criteria

Given the pragmatic nature of the study, the inclusion criteria for all participants will be:Diagnosis of probable PD according to MDS criteria [44] in staging between 1 and 3 on the Hoehn and Yahr scale [45] or diagnosis of MS according to the 2017 revised criteria of MC Donald [46] with disability level at the Expanded Disability Status Scale EDSS [47] ≤ 4.5.Age between 25 and 85 years.The preserved cognitive level at the Montreal Cognitive Assessment test (MoCA test > 15.5) [48].No rehabilitation program being implemented at the time of enrollment.Stable drug treatment (last three months) with L-Dopa or dopamine agonists (PD group) or disease modifying therapies (DMTs) (MS group).

The exclusion criteria for all participants will be:The presence of comorbidities that could hinder patients from safely participating in a home program or indicate clinical instability (e.g., severe orthopedic issues or significant cognitive impairments).Unsuitable environmental factors, such as inadequate space for rehabilitation activities or the absence of a stable internet connection.The presence of major psychiatric complications or personality disorders, assessed through a clinical interview.The presence of severe impairments in visual and/or auditory perception.Falls resulting in injuries or more than two falls in the six months prior to recruitment (for both PD and MS groups).Relapse ongoing/less than 3 months since the last relapse (MS group).The presence of “frequent” freezing as recorded at the administration of Section II (daily life activity) of the UPDRS (score ≥ 3) (PD group).EDSS-FS (cerebellar function) ≥ 3 (MS group).

### 2.5. Trial Interventions

Due to the pragmatic nature of the study and the need for open-label design to assess the effects of different TR protocols, we utilized available TR systems. Specifically, the HOMING Professional (https://www.tecnobody.com/) and KHYMEIA HOMEKIT VRRS ENGINE—Khymeia (https://khymeia.com/it/), both certified as Class I medical devices, facilitate the delivery of digital content for TR using task-oriented and impairment-oriented approaches for neuromotor rehabilitation in both synchronous and asynchronous modes.

To mitigate potential difficulties patients may face in using technologies due to unfamiliarity with the digital systems involved, all participants will receive comprehensive training at the clinical center, with caregivers present when possible. This training will cover device operation, internet connectivity issues, and space optimization for home rehabilitation.

Moreover, we harmonized the rehabilitation activities to establish the intervention protocol: a team of experts compared the exercises of the two TR systems available and included those exercises with the same rehabilitative characteristics in the rehabilitation protocol. Table 1 reported an example of a TR session. The harmonized protocol of TR intervention for people with PD and MS will be focused on addressing impairments and functional limitations that affect activities and participation in everyday life. In more detail, the neuromotor rehabilitation program for the TRsA group includes exercises designed to enhance functional mobility and physical capacity, following a task-oriented approach. The TRsA protocol focuses on functional activities to improve motor skills and coordination, grounded in motor learning principles to promote neuroplasticity [49]. By actively practicing real-world tasks, the brain adapts, strengthening existing neural pathways and creating new connections, which ultimately supports functional recovery. Specifically, the patient will be asked to perform task-oriented activities focused on controlling the center of mass while seated and/or during upright standing, in both static and dynamic conditions. All activities will be focused on the control of large body mass segments, head, eyes, and trunk coordination, and sensory reweighting. The difficulty level of the exercises will be adjusted in real time based on the patient’s performance, as recorded by the digital device used (Table 1).

Instead, the neuromotor rehabilitation program of the TRcA group integrates a combination of task-oriented exercises (designed to enhance functional mobility and physical ability) with impairment-oriented exercises (focused on muscle strength recovery, resistance training, and endurance improvement). The combined approach not only aims to foster neuroplasticity but also optimizes the recovery of motor functions and overall mobility. By targeting both functional tasks and muscle impairments, this program works synergistically to improve the patient’s overall physical capabilities. The exercises were specifically aimed at improving strength in muscles involved in maintaining balance and walking such as hip abductors, quadriceps, plantar flexors, and dorsal flexors. The difficulty level of the exercises will be modulated in real time based on the patient’s performance, as recorded by the digital device used (Table 1).

The characteristics of the TR intervention (TRsA and TRcA) in terms of frequency, intensity, time, and type are as follows: [a] in terms of Frequency, the TR group will undergo 5 weeks of intervention, with 4 sessions per week, delivered through a mixed model (3 asynchronous sessions and 1 synchronous session per week). Participants can choose the timing of each home TR session based on their preferences and needs; [b] regarding the Intensity, each session will be tailored to the patient’s functional abilities, ensuring progressive difficulty through the system’s feedback; [c] as regards Time, sessions will last approximately 50 min per day; [d] in terms of Type, TR activities will differ according to the neuromotor rehabilitation program proposed (TRsA vs. TRcA).

Finally, indications for home-based management following a conventional approach will be provided for the CeT group (placebo comparator). Specifically, we will implement the S.A.M.B.A. educational protocol in use at the IRCCS Fondazione Don Gnocchi in Milan (https://caditer.dongnocchi.it/samba-main/, accessed on 22 January 2025). The S.A.M.B.A. protocol consists of educational lessons (4 lessons per week for a total of 5 weeks) delivered via tablet-based content, covering five key topics: socialization, environmental factors, movement, psychological well-being, and alimentation. This structured program is designed to provide knowledge rather than exert a specific therapeutic effect.

